
#### Semi-structured interview

After T2 assessment, each participant will be offered the opportunity to complete a semi-structured interview with the researcher. Interviews will solicit participants’ experiences of participating in the study, with a focus on the treatment phase and assessments. These results will inform the design of a future RCT of OTRTR.

#### Secondary outcomes

The secondary outcome measures relate to intended treatment outcomes of OTRTR. The following measures will be completed at baseline (T0), post treatment (T1), and 3-month follow-up (T2) by a researcher blind to the participant’s allocation status.Birchwood Insight Scale (BIS) [14] is an eight-item self-report measure of insight. The original study established BIS total score test-retest reliability (1-week) as *r* = 0.90 and internal consistency of *α* = 0.75. The BIS variable used in this study will be the total score (max 12).Coping Styles Questionnaire (CSQ) [15] is a 60-item self-report measure on the use of maladaptive and adaptive coping styles. It is comprised of four subscales, each a unique dimension of coping: rational, detached, emotional, and avoidance. Test-retest reliability of the CSQ subscales range from *r =* 0.70 to 0.80, and the subscale internal consistencies of *α* = 0.69 to 0.90. The CSQ variable used in this study will be the total of the two adaptive coping subscales, Rational and Detached.Clinical Outcomes in Routine Evaluation Outcome Measure (*CORE-OM*) [28] is a 34-item self-report measure of psychological distress that covers four domains: wellbeing, symptoms/problems, functioning, and risk to self and others. A global measure of distress is also calculated across these domains. Good psychometric properties for this measure in non-clinical, clinical, and forensic populations have been established [19, 29]. The CORE-OM variable used in this study will be the 34-item mean score (max 4).Rosenberg Self-Esteem Scale (RSE) [30] is a 10-item self-report measure of self-esteem. The RSE has an internal consistency of *α* = 0.77 and two-week test-retest reliability of *r* = 0.85. The total RSE score will be used (max 30).Questionnaire on the Process of Recovery (QPR) [31] is a 22-item measure of service user-rated recovery comprised of an interpersonal and intrapersonal subscale. The initial validation study found acceptable two-week test-retest reliability (intrapersonal subscale *r* = 0.87, interpersonal subscale *r* = 0.77) and internal consistency (intrapersonal *α* = 0.94, interpersonal *α* = 0.77). The intrapersonal (max 68) and interpersonal (max 20) subscale scores will be used.Brief Psychiatric Rating Scale (BPRS) [32] is a clinician/researcher-rated tool used to assess severity of psychopathology. The 18 items sum to derive a continuous total score of symptom severity. The BPRS has good psychometric properties is the most widely used outcome measure in treatment studies across populations with severe and persistent mental illness [33]. The total BPRS score will be used (max 126).Institution-recorded incidents of physical aggression and violence: The number of incidents of violence/aggression, for which the participants are considered to have responsibility in instigating or exacerbating, during the study treatment phase and 3-month follow-up period will be compared across treatment groups. This information will be as participants complete T2.Institutional privileges: Changes in institutional privileges (e.g., increased grounds access, unsupervised phone calls, and patient outings) will be recorded for all participants during the study treatment phase and 3-month follow-up period. This information will be after participants complete T2.

#### Weekly clinical measures

Following an intensive longitudinal methods (ILM) approach [7, 8], the BIS and CSQ will be administered to all participants each week during the 12-week study treatment phase. Members of the local health care team will administer these weekly measures and as such they will not be blind to participants’ treatment allocation status.

### Participant and data retention

Participants may withdraw from the study at any time. We will offer participants who choose to withdraw from the study the opportunity to share their views and reasons for withdrawal in a post-study interview at the time of their exit from the study. Participants will be reassured that this is voluntary, and they need have no further contact with the research team. Discontinuing OTRTR therapy will not exclude participants from the study. Participants who wish to discontinue OTRTR will be offered the opportunity to participate in the regular assessment points should they wish. Participants who withdraw from the research study will be able to continue (if in OTRTR condition) or commence (if in TAU condition) OTRTR in the context of their usual care and treatment. Measures will be clearly prioritized so that in all assessment batteries primary measures will be administered prior to secondary minimizing the loss of primary data should participants withdraw during an assessment session. The assessment battery may be completed over two sessions to avoid participant testing fatigue.

### Protocol amendments

Any modifications to the protocol that may impact on the conduct of the study will require a formal amendment to the protocol. Such amendments will be agreed upon by the trial research team, and approved by NHS Scotland Research Ethics Committee prior to implementation, and notified to the local research committees of participating organizations in accordance with local regulations. Minor corrections and/or clarifications to the protocol, including administrative changes that have no effect on the way the study is to be conducted, will be agreed upon by the trial research team and documented. NHS Scotland Research Ethics may be notified at the discretion of the trial research team. The ISRCTN trial registration will also be updated to reflect any protocol amendments made.

### Data management

All research-generated data will be entered into password-protected electronic spreadsheets and stored separately from any participant identifying information. Participants will be assigned unique study IDs. A master list matching participant names and study IDs will be kept in a password-protected excel document and stored on a secure NHS drive. Only members of the trial research team will have access to the master list. Original forms (e.g., questionnaires) will be retained for a period of 3 years after completion of the study, stored securely on NHS Scotland premises. Anonymized data files may be retained indefinitely by the research team. To ensure accurate data collection, the optional post-study interviews will be audio recorded and transcribed for qualitative analysis. Audio data will be collected using an encrypted password-protected audio recorder and uploaded to a secure NHS drive. Data entry, preparation, and analysis will be carried out using a bespoke standardized operating procedure to ensure data integrity.

### Statistical analysis

#### Feasibility and acceptability outcomes

Descriptive statistics will be reported for the key outcomes on the feasibility data (including mean averages, standard deviations, and ranges where appropriate). The number of patients who were eligible, recruitment into the study, and attrition rates according to each intervention arm will be considered using descriptive statistics and reported using the CONSORT (Consolidated Standards of Reporting Trials) flow chart (Fig. 1). Interviews will be analyzed using thematic analysis [34] to identify emerging themes within the data.

#### Clinical outcomes

This study will not be sufficiently powered to determine treatment efficacy. Evidence of change on clinical outcomes will be considered with a focus on effect sizes and reliable change indices over null hypothesis significance testing. Effect size estimates (Cohens’ *d*) will inform sample size estimates and inform decisions regarding the most appropriate outcome measures for use in a future phase III trial of OTRTR. A modified intention to treat (ITT) analysis will be used to analyze change on the outcome measures and derive the effect size estimates. Therapeutic effect sizes (with 95% confidence intervals) will be derived using linear regression models comparing T1 scores for the two treatment arms, with baseline (T0) scores included as covariates. These analyses will be repeated using between-group comparison of means at T2 for estimated maintenance of treatment effects.

Similarly, effect sizes for change in institutional violence/aggression will be derived. The mean number of incidents of violence/aggression (recorded by the institution) measured at post treatment (the mean number of incidents for duration of study treatment phase, up to T1) will be compared, controlling for baseline differences (the mean number of incidents for the 3-months preceding treatment, up to T0). This analysis will be repeated using between-group comparison of mean incidents during follow-up period (record from T1 to T2) for estimated maintenance of treatment effect.

Changes in institutional privileges (e.g., increased grounds access, unsupervised phone calls, and patient outings) will be recorded for participants in both groups throughout the study treatment phase (T0 to T1) and follow-up period (T1 to T2). To the researchers’ knowledge, this type of outcome has not been previously studied in treatment evaluations in forensic settings. This data will be examined primarily to identify the types of changes that occur and will be used to inform secondary outcome measure selection and refinement in a future definitive RCT. Descriptive statistics will be calculated and examined.

An exploratory analysis will also estimate the individual-level effects on the two primary clinical outcome measures (Birchwood Insight Scale and the Coping Styles Questionnaire). This analysis will use the weekly BIS and CSQ scores collected during the study treatment phase and analyze change using multilevel modeling (also referred to as linear mixed effects modeling). The multilevel approach is advantageous as it accounts for dependencies among observations (repeated assessments) nested within individuals and is flexible in the presence of missing data. The analysis will reveal individual trajectories (e.g., a timecourse of therapeutic effect) and variability throughout the treatment period. The model will include two levels: participants and time (repeated observations), where time is nested within each participant. Level of treatment need (assessed at baseline) will be an additional model parameter. As for the between-group analyses which aim to estimate treatment effects, this individual-level treatment effects analysis will not be sufficiently powered for definitive hypothesis testing and results will be interpreted with caution.

To our knowledge, there is no recommended Minimal Clinically Important Difference (MCID) for this study’s primary outcome measures in forensic psychiatric populations: the Birchwood Insight Scale and the Coping Styles Questionnaire. Results from this study will be used to better understand what an appropriate MCID would be for this measure in this population. We will adopt a distribution-based approach, which compares change on the outcome measure to an index of the measure’s variability [35, 36]. This approach assumes that the outcome measure change score equivalent to a small effect size (e.g., Cohen’s *d* = 0.2) would be the MCID. The MCID will be calculated multiplying 0.2 by the standard deviation of the outcome measure across the feasibility study’s entire sample at baseline.

When data is missing, we will record reasons why missing data occurred, which will help to formulate assumptions about the missing data (e.g., missing at random) for the purpose of analysis. We will use a model-based multiple imputation method to address any missing outcome, though the exact method will be selected after a survey of the pattern of missing data.

Using the standardized recording forms completed by the therapy facilitators, each therapy session will be retrospectively coded as focusing primarily on either (1) building insight or knowledge of mental health or (2) developing coping skills. In a separate model restricted to only OTRTR condition participants, therapy session focus (measured using the standardized recording forms completed by the OTRTR facilitators) will be further included as an additional predictor of change on the clinical outcome measures.

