## Methods

### Design

This study is a feasibility study using a parallel-group randomized outcome blinded design to compare OTRTR to treatment as usual (TAU). As a feasibility study, the primary study aims relate to testing the acceptability and feasibility of key trial procedures that would be necessary for a full-scale RCT of this program. The comparator group will receive treatment as usual. In this study, 50% of participants will be randomized to commence OTRTR immediately for approximately 12 weeks. The remaining 50% will engage in TAU for 12 weeks and may complete OTRTR in the future. Participants will continue their usual access to concomitant therapies and therapeutic activities throughout the study. Participants will complete a range of self-report measures and a clinical interview at baseline (T0), post treatment (T1), and at follow-up (T2), 3-months after the T1 assessment, with an assessor who will be blind to participants’ allocation status. Clinical effect sizes will be estimated using two approaches, at the group level for a range of clinical outcomes by comparing change from pre to post treatment and at the individual level for the two primary outcomes—insight into mental disorder and use of adaptive coping skills—using intensive longitudinal methods (ILM) [7, 8]. Findings from two large treatment evaluations, the PEPS trial [9] and Ministry of Justice’s evaluation of the prison-based Core Sex Offender Treatment Programme [10], demonstrated that psychological therapies have the potential to cause harm to patients, a concept which has received little attention until recently. Accordingly, this study will pilot an adverse event monitoring plan to estimate the safety of OTRTR for participants.

Following participation in the study, participants will be offered the opportunity to complete a semi-structured interview which will gather qualitative information on their experiences of participating and views on different aspects of the trial (for instance, randomization, treatment, and assessments).

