### Study setting

Participants will be recruited and identified from forensic mental health services which are part of the NHS Scotland. Services include high, medium, and low secure inpatient settings as well as community forensic teams.

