### Description of the intervention

#### On the Road to Recovery

The OTRTR program is comprised of two brief treatment modules: *Awareness & Recovery* (A&R) and *Looking After Yourself* (LAY). A&R provides psychoeducational material adapted from Morrison et al. [16] “Think you’re crazy? Think Again” and from “Coping with Mental Illness” [17], the original psychoeducation program delivered across the Forensic Network. The LAY program’s core aim is to help patients develop basic coping skills to manage psychological distress and to develop a “toolkit” for coping with this distress now and in the future. The protocol is semi-structured and organized by topics instead of sessions, which allows the program to flexibly match pace to groups with greater or lesser need by adjusting the number of sessions. Each topic contains several objectives that are accompanied by structured didactic activities, exercises, and discussion prompts. The program will run over approximately 12 weeks, with weekly 2-h sessions. Treatment delivery is primarily in small groups; however, the program can also be delivered on an individual basis as part of the study. Participant attendance and engagement in the treatment sessions will be monitored and recorded. Participants’ RMOs may withdraw a participant from the study and therefore discontinue OTRTR sessions should there be a deterioration in participants’ clinical presentation.

OTRTR therapy facilitators will receive group supervision at least once every four sessions delivered, consistent with the Forensic Matrix governance standards [18]. Facilitators will be provided with standardized recording documents to closely record the program content delivered in each session.

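### Aggression incidents are compared as mean counts up to T1 with no allowance for time observed, and T1 is not tied to the same week in both arms

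*Protocol article*

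**What the plan says.** The Clinical outcomes part of the Statistical analysis section first describes linear regression of T1 scores on arm and baseline, with Cohen's d. It then says that effect sizes for aggression will be derived similarly.

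- **Quantity compared:** "the mean number of incidents for duration of study treatment phase, up to T1".
- **Baseline adjustment:** "the mean number of incidents for the 3-months preceding treatment, up to T0".
- **Follow-up:** the comparison is repeated with mean incidents between T1 and T2.

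The Secondary outcomes section likewise speaks of the number of incidents. Neither section mentions a rate, an offset or person-time.

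On the length of the window, the Design section says that "50% of participants will be randomized to commence OTRTR immediately for approximately 12 weeks", whereas for the other arm "The remaining 50% will engage in TAU for 12 weeks". The On the Road to Recovery section plans weekly sessions organized by topic, which "allows the program to flexibly match pace to groups with greater or lesser need by adjusting the number of sessions". The Participant timeline section places T1 after treatment in both arms without giving a week. That section and Weekly clinical measures both describe the treatment phase as 12 weeks long.

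**The concern.** A mean count is comparable between arms only if the arms are observed for the same time. Here the end of the window is the post-treatment assessment. Treatment length is flexible in one arm and stated as 12 weeks in the other, so any departure from 12 weeks would be tied to allocation. The baseline covariate cannot remove this, because its 3-month window is the same for everyone. Participants who leave early also contribute a shorter window, which matters for the comparison if leaving differs by arm.

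Two uses of the result are at stake. The article says its effect sizes will inform sample size estimates and the choice of outcome measures for a phase III trial. Its Design section also stresses that psychological therapies can cause harm, so a shift in incident counts produced by scheduling could be misread as a signal in either direction.

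The article already uses the idea of a rate elsewhere: in Primary outcome measures, serious adverse events are to be compared with each participant's rate in the 12 weeks before enrolment.

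**Working it through.** The article gives no incident rate, dispersion or effect size for this outcome, so there is no figure of its own to reproduce.

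**Inputs from the article:** TAU phase 12 weeks; OTRTR phase about 12 weeks, number of weekly sessions adjustable; baseline window 3 months in both arms; 25 per arm. **Assumed:** OTRTR phases of 10 to 16 weeks, incident rates, and dispersion.

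**Step 1: ratio of mean counts.** The expected count is weekly rate × weeks observed. With the same true rate in both arms, the ratio is (OTRTR weeks)/12:

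| OTRTR weeks (assumed) | Ratio of mean counts |
|---|---|
| 10 | 10/12 = 0.83 |
| 12 | 12/12 = 1.00 |
| 13 | 13/12 = 1.08 |
| 14 | 14/12 = 1.17 |
| 16 | 16/12 = 1.33 |

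**Step 2: spurious Cohen's d.** For negative binomial counts with mean m and dispersion k, the variance is m + m²/k. With m = 1 per 12 weeks, k = 1 and OTRTR at 14 weeks, the OTRTR mean is 1.167. The variances are 2.00 (TAU) and 1.167 + 1.361 = 2.528 (OTRTR), so d = 0.167/√((2.00 + 2.528)/2) = 0.167/1.505 = 0.11. Over rates of 0.25 to 2 per 12 weeks, and dispersion from k = 0.3 to Poisson, the ranges are:

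- 10 weeks: −0.07 to −0.25
- 14 weeks: +0.06 to +0.23
- 16 weeks: +0.11 to +0.44

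**Step 3: does baseline adjustment help, and does a rate?** Simulation with 25 per arm, true rate 1.0 per 12 weeks in both arms, k = 0.5, linear regression on arm and a 13-week baseline count, 4,000 replicates:

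| OTRTR weeks | Adjusted difference, raw counts | Adjusted difference, counts per 12 weeks |
|---|---|---|
| 10 | −0.16 | −0.01 |
| 12 | 0.00 | 0.00 |
| 14 | +0.15 | −0.01 |
| 16 | +0.31 | 0.00 |

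Baseline adjustment leaves the artefact in place. Dividing by time observed removes it.

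**Step 4: size against the noise.** With a lower rate (0.5 per 12 weeks), strong overdispersion (k = 0.3, about 75% of participants with no incident) and 22 per arm, the spurious difference is about +0.04 at 13 weeks, +0.07 to +0.09 at 14 and +0.15 at 16, over repeated runs. The standard error is 0.26 to 0.29, so the bias is about a quarter of a standard error at 14 weeks and half at 16. Coverage of the 95% interval is about 95% at 13 and 14 weeks and 92% to 94% at 16.

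**The case against.** The strongest reply is that two sections describe a 12-week treatment phase, and incidents are counted over that phase. If T1 falls at week 12 in everyone, the windows are equal and no length bias arises. That is correct, but no section says T1 is held there when OTRTR finishes earlier or later, and the Design and intervention sections point to a flexible end. The passages need reconciling.

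Several stronger readings are tempting and are not supported:

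- **That OTRTR will look more violent.** The program can "flexibly match pace to groups with greater or lesser need by adjusting the number of sessions", so it may run shorter as well as longer. The sign is unknown.
- **That the distortion is large.** Nothing in the article suggests a 16-week phase. At 13 or 14 weeks the bias is small against the standard error and interval coverage is close to nominal.
- **That community participants would be counted as zeros.** The Study setting section lists "low secure inpatient settings as well as community forensic teams", but no section says how their incidents are recorded.
- **That the follow-up window is biased by design.** T2 is 3 months after T1 in both arms, so no difference in length is planned there. Stopping OTRTR does not by itself end participation either (Participant and data retention).
- **That a linear model for counts is fixed.** It is inferred from the word linking this outcome to the questionnaire analysis; the count model is not named.

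It is also fair to say that the model is normally a matter for the analysis plan, which is not shown. What remains is that the article itself states the quantity to be compared, and that quantity has no time denominator.

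**Conclusion.** The point holds in a conditional form. As written, the aggression comparison can confound incident rate with time observed, because only one arm has a flexible treatment length and T1 is not tied to a week. With equal true rates, the ratio of mean counts departs from 1 in proportion to OTRTR weeks/12, in either direction. Under most assumed rates and dispersions the spurious d is modest. Only the upper part of the range reaches 0.2, the value the article takes as the minimal important effect for its insight and coping measures. The treatment-length bias is zero if T1 is held at week 12 in both arms; unequal early leaving would still need handling.

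All durations, rates and dispersions used here are assumptions. The outcome is secondary, the trial is not powered for efficacy, and aggression is not among the progression criteria, so this is minor to moderate.

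**What to change.** In the Clinical outcomes part of the Statistical analysis section, replace the comparison of mean incidents with a comparison of incidents per person-week observed, separately for T0 to T1 and T1 to T2. Adjust for the baseline incident rate per week, and report a rate ratio or rate difference with a 95% interval. A quasi-Poisson model with a log person-time offset and robust standard errors, containing arm and baseline rate only, would serve.

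Alternatively, count incidents over one fixed window of equal length from randomization in both arms. Either way, state when T1 falls if OTRTR does not end at week 12, so that the sections agree.

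A fuller negative binomial model with site terms should not be required. In a check with 75% zeros and four assumed sites, 37% to 46% of fits failed or gave unusable standard errors.

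The cost is a change of analysis wording and the use of each participant's observation start and end dates, including the withdrawal date for those who leave. The article does not say these dates are held for analysis, so that should be confirmed. Estimates will be imprecise with few events, and a rate ratio may be inestimable if an arm has none, in which case the rate difference should be given.
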